## Methods

### Aim, design and setting

We hypothesize that in patients with sub-acute spastic hemiparesis after stroke, practice restricted to the active control zone (personalized training) combined with excitatory a-tDCS will improve control over the range of ST regulation in the elbow and improve UL kinematic and clinical performance measures compared to non-personalized training with a-tDCS and personalized training with sham-tDCS. We propose a single-blind, parallel, three-group, randomized controlled trial (RCT; allocation ratio 1:1:1) involving personalized therapeutic intervention to improve control over the range of regulation of STs with the application of excitatory a-tDCS, which, under generally facilitatory conditions (e.g., motivating patients with VR games), may strengthen remaining connections and help restore inter-hemispheric balance. The Standard Protocol Items: Recommendations for Interventional Trials (SPIRIT) flow diagram of study enrollment, interventions and assessments is shown in Fig. 2. In addition, the implementation of such training programs in a low-to-middle-income country will be investigated by including four academic rehabilitation centers in Canada, Israel and India.

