### Participants and recruitment

Sixty people with sub-acute spastic hemiparesis after stroke will be recruited during their hospitalization in rehabilitation centers. In order to achieve adequate participant enrollment, constant chart review of newly admitted patients will be done. Individuals will be included if they have/are: (1) a stroke in the middle cerebral territory, confirmed by magnetic resonance imaging/computed tomography (MRI/CT), and medically stable; (2) aged 25–80 years; (3) in the sub-acute stage of stroke (3 weeks to 6 months post stroke); (4) arm paresis (2–6/7 on the Chedoke-McMaster Stroke Assessment arm score, CMSA [17]) and able to perform at least 30° elbow flexion and extension; (5) elbow flexor and/or extensor spasticity (>1 + out of 4 on the Modified Ashworth Scale, MAS [18, 19]); and (6) able to provide informed consent. Exclusion criteria are: (1) other major neurological or neuromuscular/orthopedic problems or pain interfering with results’ interpretation; (2) medical co-morbidities such as HIV/AIDS, etc.; (3) major cognitive deficits (˂ 20 on the Montreal Cognitive Assessment, MoCA [20]); (4) history of psychiatric disorders, alcohol or drug abuse, seizures, migraines, metal in the cranium, and cochlear and cardiac implants; (5) taking medications (e.g., anti-epileptic and psychoactive drugs) that could affect brain activity [21, 22]. Criteria for discontinuation include participant request or adverse events.

Eligibility will be established by a blinded research coordinator. Participants will provide informed consent and be allocated to one of three treatment groups (*n* = 20 per group) by permuted block randomization, balanced for age (25–50 years/51–80 years) and chronicity (3–12 weeks/13–24 weeks). Participants will receive a training and evaluation schedule, and participation will be monitored by the study coordinator, who will also provide reminders to attend scheduled activities. Travel expenses will be remunerated for follow-up visits.

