The sample size is based on preliminary data showing that the mean change in elbow-flexor ST angle was 10° in stroke subjects with spasticity who underwent 2 weeks of transcutaneous electrical nerve stimulation treatment compared to 2° after sham stimulation (unpublished data). Considering an *α* level of 5% and a 95% power (effect size = 2.23) to detect differences using a mixed-design 3 × 3 analysis of variance (ANOVA) (G*Power 3.1.1), the minimal sample size is 13 subjects per group. Sample size was increased to 18 per group to have an equal number of subjects per group per site (six per group, per site). We will recruit 20 subjects per country overall considering a dropout rate of 10–15% for a final cohort of 60 subjects.

Prior to the start of recruitment of participants, standardized procedures will be established to ensure consistency across sites. Intervention therapists will receive training guidelines and evaluators will receive screening and clinical assessment documents. In addition, all team members directly involved in data collection will have face-to-face training on data collection protocols. Quarterly online meetings will be scheduled to maintain adherence to the protocols across sites.

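### Sixty is the number enrolled, not the cohort left after 10–15% dropout; it covers the 18-per-group target only at 10% loss, and six per group per site is not assured

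*Protocol article*

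**What the plan says.** All the figures are in the protocol article, mostly under Participants and recruitment.

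- Enrolment: "Sixty people with sub-acute spastic hemiparesis after stroke will be recruited during their hospitalization in rehabilitation centers". Participants are then to "be allocated to one of three treatment groups", with 20 given for each. Aim, design and setting gives the "allocation ratio 1:1:1".
- Power-based minimum: "the minimal sample size is 13 subjects per group".
- Increase for site balance: "Sample size was increased to 18 per group to have an equal number of subjects per group per site (six per group, per site").
- Dropout allowance: "We will recruit 20 subjects per country overall considering a dropout rate of 10–15% for a final cohort of 60 subjects".
- Setting, under Aim, design and setting: "four academic rehabilitation centers in Canada, Israel and India".

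**The concern.** The last step of the sample size paragraph names a dropout rate and then a final number. Read in order, it says that 60 are left once dropout has been allowed for. But 60 is also the number recruited, both in the opening sentence of the section and as 20 in each of three countries. One figure cannot be both the intake and the remainder when 10–15% are expected to be lost.

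Two stated quantities depend on this step: 18 per group, and six per group per site, which is the only reason given for going above 13. If the recruitment figure does not deliver them over the stated dropout range, the article describes a better-filled and better-balanced trial than its own numbers support. At stake is whether the sample size statement is accurate. The power claim rests on 13 per group.

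**Working it through.** **Inputs.** From Participants and recruitment: 60 enrolled, 20 per group, 20 per country, target 18 per group, dropout 10–15%, minimum 13 per group. From Aim, design and setting: three arms at 1:1:1, four centers in three countries.

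**1. Reproduce the plan's figure.** Target total = 18 × 3 = 54. Enrolment needed = target / (1 − dropout).

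- At 10%: 54 / 0.90 = 60. This reproduces the stated 60 exactly.
- At 15%: 54 / 0.85 = 63.5, so 64. With equal groups, 18 / 0.85 = 21.2, so 22 per group and 66 in total.

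So 60 is the enrolment figure obtained by inflating 54 at the lower end of the range.

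**2. What 60 enrolled leaves.** Remaining = 60 × (1 − dropout).

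| Dropout | Remaining | Per group | Per group per country |
|---|---|---|---|
| 10% | 60 × 0.90 = 54 | 18 | 6.0 |
| 12.5% | 60 × 0.875 = 52.5 | 17.5 | 5.8 |
| 15% | 60 × 0.85 = 51 | 17 | 5.7 |

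The shortfall against 54 runs from 0 to 3 participants, or 0 to 1 per group.

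These are averages. If losses are independent between participants (an assumption), the chance that all three groups keep at least 18 of 20 is about 31% at 10% loss and about 7% at 15%. The chance that all three keep at least 13 is above 99% and about 98% respectively.

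**3. Six per group per site.**

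- If site means country: 20 / 3 = 6.67, so the most even split at enrolment is 7, 7 and 6. A 10% loss is two participants per country. Six in every arm results only if one is lost from each arm of seven. If the two losses fall at random, there are 7 × 7 = 49 favourable pairs out of 20 × 19 / 2 = 190, about 26% per country.
- If site means center: 6 × 3 arms × 4 centers = 72, more than the 60 enrolled. Sixty allows 60 / 12 = 5 per group per center.
- Six per group per site gives 18 per group only with three sites (6 × 3 = 18), so the sentence appears to use site for country.

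**4. Effect on the stated power.** The minimum is 13 × 3 = 39. Sixty enrolled stays at or above 39 up to a loss of 1 − 39/60 = 35%. At the worst stated dropout, 17 per group remain, four above the minimum.

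**The case against.** The strongest reply is that the allowance is sound and only one phrase is loose. Fifty-four divided by 0.90 is exactly 60, the section says that sixty will be recruited, and the disputed sentence itself opens with recruiting 20 per country. On that reading 60 is plainly the enrolment, and the worst case is one participant per group below a target chosen for balance, not for power. Most of this stands. It rules out calling the allowance simply wrong, and it keeps the consequence small. It does not make the sentence correct: 60 is still labelled as the final number after dropout, and the upper part of the stated range is still not covered.

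Two stronger readings are tempting, and the article does not support either.

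- A reader might infer that 60 completers are promised and that the trial will fall six to nine short. The fixed recruitment of sixty, at 20 per group, shows that 60 means enrolled.
- A reader might infer that sites will replace dropouts to reach 60, and that this would break the intention-to-treat principle in Statistical analyses. The article nowhere mentions replacement. Nor would replacement by itself breach intention-to-treat, provided that added participants were randomised and those who left stayed in the analysis.

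**Conclusion.** The point holds as an inconsistency in the stated sample size, with modest consequences. Sixty is the number enrolled and randomised. After the plan's own 10–15% dropout, 51–54 are expected to remain, 17–18 per group. The target of 18 is met on average at 10% loss and missed by up to one per group at 15%. Six per group per site is not assured on a country reading, and cannot be reached with 60 participants on a center reading.

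The stated power is not affected on the protocol's own terms, because 17 exceeds 13. This takes the minimum of 13 as given; whether it follows from the stated effect size is a separate question, not examined here. The conclusion also assumes that dropout is spread evenly over groups and countries. Uneven loss would leave some cells smaller and others larger without changing the totals.

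**What to change.** In the sample size paragraph, replace the closing phrase about the final cohort with:

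*60 participants will be enrolled and randomised (20 per group, about 20 per country); with 10–15% dropout, 51–54 (17–18 per group) are expected to complete.*

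Restate the site-balance sentence as an approximate target per country, for example *about six completers per group in each country*. This keeps the stated reason for going from 13 to 18 and removes the clash with four centers. The sponsor should confirm that site was meant as country.

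The cost is wording only. The reported number becomes slightly less favourable. Enrolment, randomisation and analysis do not change, and no additional participants are proposed.

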### Intervention

Participants will enroll in a 10-day training program over two consecutive weeks (5 days per week). Outcome evaluators, statistical analysts and care providers will be blind to group assignment but not the intervention therapists, given the nature of the intervention. Intervention therapists will receive allocation information from the study coordinator via coded email. Participants will be randomly allocated as follows: (group 1) personalized training (reaching within determined active control zones) and a-tDCS over the affected hemisphere; (group 2) non-personalized training (reaching in both spasticity and active control zones; full active ROM) and a-tDCS over the affected hemisphere; and (group 3) personalized training and sham-tDCS.

Prior to the reaching training, elbow-flexor STs in the hemiparetic arm will be determined in each participant to identify the active control zone, using the Montreal Stretch Reflex Threshold device (MSRT; [23] see below). For the personalized training groups (groups 1 and 3), elbow extension will be restricted to the active control range using a range-restriction elbow brace (Breg Inc., Carlsbad, CA, USA) blocking elbow extension beyond the permitted ST. Participants in the non-personalized training group will wear the brace, but elbow ROM will not be restricted. All participants will have partial arm-weight support with a sling during the training to avoid fatigue. Since a goal of the training is to increase isolated elbow extension, the sling will be placed so that the weight of the upper arm and shoulder is supported without restricting elbow movements. The support will be provided throughout the training sessions for all subjects so that training parameters are equivalent across groups and sites.

During reaching training, participants will sit on an armless chair and make discrete arm reaches towards targets displayed at various locations in the three-dimensional (3D) workspace with unrestrained trunk movement. Training will be guided by a physical or occupational therapist for 50 min (actual movement time) per day. Four interactive games from the Jintronix VR system (Montreal, QC, Canada) will be viewed on a large screen. Three activities will involve unimanual movement and one will involve a bimanual activity (Fig. 3). The total amount of movement time each training day will be recorded by the Jintronix system. Treatments will be matched for both duration and intensity across sites.

**Fig. 3 Fig3:**
[figure not shown]
Jintronix virtual reality (VR) games used in the intervention. **a** Fish Frenzy game requires the player to trace a three-dimensional (3D) trajectory by moving a fish on the screen in different shapes. **b** Kitchen Cleanup game requires forward reaching towards kitchen cutlery and returning them to shelves and drawers. **c** Garden Grab game requires lateral reaching while planting seeds, harvesting and transferring tomatoes to baskets. **d** Catch, Carry, Drop game requires bilateral coordination while catching apples, carrying and dropping them into a container

#### Calibration and game progression

In the personalized practice group, the Jintronix system will be calibrated prior to each training session according to the individual’s ability to reach within the active zone only, whereas in the non-personalized practice group the calibration will be done based on the individual’s full active ROM. In this way, the calibration procedure is used to set and progress the sagittal reaching distance in each game from near to far according to the length of the subject’s effective sagittal reaching distance. Success in each reaching task depends on a combination of reaching distance, speed and precision according to Fitts’ law [24]. Thus, difficulty levels of each activity will be increased by altering the location of the virtual targets and by decreasing the allowable movement time to complete each reach (i.e., by increasing movement speed), while target size remains the same. Levels will be progressed when the participant reaches at least 95% success rate in three rounds. Game difficulty will be progressed according to the Challenge Point Theory of motor learning [25]. This theory suggests that learning is enhanced by optimally challenging the individual through manipulation of task difficulty according to their motor skill level and cognitive capacity. Since learning is also affected by performance-related feedback, participants will receive concomitant visual and auditory Knowledge of Results about task success when movements are made accurately and within a specified lapse of time programmed by the therapist. Participants will also receive negative Knowledge of Performance about the use of compensatory trunk movements during reaching through the Jintronix system. Thus, if the participant leans their trunk more than 5° in the sagittal direction, a yellow square will appear on the screen and a reach success will not be registered. The 5° trunk-flexion range was chosen since it corresponds to the cutoff value identified in Subramanian et al. [26] as indicating compensatory trunk movement. Regardless of the training zone and difficulty level, all participants in each group will follow the same training guidelines and complete the 50 min of active movement time.

A-tDCS (Soterix, New York, NY, USA) will be provided by a constant direct current stimulator at an intensity of 1.5 mA, applied via saline-soaked surface electrodes (5 cm × 7 cm) on the scalp. Stimulation will occur during the initial 30 min of the 50-min training session. The anode will be placed over the sensorimotor areas of the affected hemisphere (placed over C3/C4 using the electroencephalogram (EEG) 10–20 referencing system), while the cathode will be placed on the contralateral supraorbital area. For the sham stimulation, the same electrode placement will be followed, but the device pre-programmed sham setting will apply stimulation only for the first minute. In the first 30 s, a stimulation ramp-up is expected to cause a mild itching sensation underneath the anodal electrode. This sensation is expected to fade between 40 and 60 s, at the end of which the intensity reaches zero level. No stimulation will be provided for the rest of the practice session.

As this trial intervention is carried out in different centers, the adherence to the intervention will be ensured by recording the frequency and the intensity of the games on standardized documents, supervision by the lead investigator at each site and supervision by the co-principal investigators (PIs) via regular meetings.

### Study outcomes

Outcome measures will be documented before (Pre), after 10 days of intervention (Post) and 1 month after intervention end (Follow-up). Measures will be used to obtain an overall clinical profile of arm and hand impairment and function. Arm motor recovery will be evaluated at two levels of the International Classification of Function: Body Structure and Function (motor impairment) and Activity [27]. The primary outcome will be the ST angle and the ratio between the range of the biceps spasticity zone and the full biomechanical elbow-extension ROM.

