**Methods:**

This single-blind randomized controlled trial will take place at four academic rehabilitation centers in Canada, India and Israel. The intervention involves 10 days of personalized VR reaching training with both groups receiving the same intensity of treatment. Participants with sub-acute stroke aged 25 to 80 years with elbow spasticity will be randomized to one of three groups: personalized training (reaching within individually determined active control zones) with a-tDCS (group 1) or sham-tDCS (group 2), or non-personalized training (reaching regardless of active control zones) with a-tDCS (group 3). A baseline assessment will be performed at randomization and two follow-up assessments will occur at the end of the intervention and at 1 month post intervention. Main outcomes are elbow-flexor spatial threshold and ratio of spasticity zone to full elbow-extension range. Secondary outcomes include the Modified Ashworth Scale, Fugl-Meyer Assessment, Streamlined Wolf Motor Function Test and UL kinematics during a standardized reach-to-grasp task.

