#### Assessment of spasticity and active control zones

Since active elbow extension (active control zone) is limited by the location of the ST in the angular range of the elbow, the ST angle of the elbow flexors (biceps brachii, BB) will be measured. This will allow us to determine the range of angles in which BB cannot be relaxed (spasticity zone) and the range in which reciprocal agonist/antagonist muscle activation is possible (active control zone). The ST angle will be defined using the MSRT, a portable clinical device consisting of a two-channel electromyography (EMG) system (Procomp 5, Thought Technology, Montreal, QC, Canada), an electrogoniometer (servo-type rotational-position potentiometer P2200; Novotechnik U.S. Inc., Southborough, MA, USA) and dedicated software implemented on a laptop computer (Fig. 4). The MSRT has moderate-to-good intra- and inter-evaluator reliability for the measurement of elbow spasticity in post-stroke participants [23].

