### Statistical analyses

Descriptive statistics will be used to highlight main demographic and clinical characteristics of participants. After verification for linearity, normality and homoscedasticity, parametric mixed-model ANOVAs will be used to determine which stimulation and practice modality combinations lead to greater improvements. The mixed-model analysis will include one between-subject factor – group with three levels (personalized training + a-tDCS, non-personalized training + a-tDCS and personalized training + sham-tDCS), and one within-subject factor – time with three levels (Pre, Post and Follow-up). Multiple linear regression analyses on pooled data will identify relationships between primary outcomes and changes in clinical and kinematic measures. If assumptions for parametric tests are not met, non-parametric tests will be substituted. Results will be analyzed based on intention-to-treat principles. Individual participation in other in-patient services will be documented (physiotherapy, occupational therapy, speech therapy, social work, recreation, other) and compared between sites to account for effects of usual-care exposure. Results will be disseminated to individuals, user groups, health care and research professionals at trial completion.

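### Two unranked primary outcomes, no primary visit, and an omnibus group x time ANOVA that cannot by itself show that personalised training + a-tDCS beats both comparators

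*Protocol article*

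**What the plan says.** All places are in the protocol article.

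- **Outcomes.** Study outcomes: "The primary outcome will be the ST angle and the ratio between the range of the biceps spasticity zone" and the full range. The abstract lists the same pair without ranking: "Main outcomes are elbow-flexor spatial threshold and ratio of spasticity zone to full elbow-extension range".
- **Overlap.** Assessment of spasticity and active control zones says of the ST measurement: "This will allow us to determine the range of angles in which BB cannot be relaxed (spasticity zone". The numerator of the ratio is therefore derived from the first primary outcome.
- **Visits.** "Outcome measures will be documented before (Pre), after 10 days of intervention (Post) and 1 month after intervention end (Follow-up". Neither post-treatment visit is called primary.
- **Hypothesis.** Aim, design and setting expects the combined arm to improve more "compared to non-personalized training with a-tDCS and personalized training with sham-tDCS".
- **Analysis.** Statistical analyses plans mixed-model ANOVAs with group (three levels) and time (three levels) "to determine which stimulation and practice modality combinations lead to greater improvements". It names no effect, contrast or success rule.
- **Sample size.** Participants and recruitment uses the change in ST angle only, with a single 5% alpha.
- **Arm labels.** The abstract's three groups read "with a-tDCS (group 1) or sham-tDCS (group 2), or non-personalized training" with a-tDCS. The Intervention section has "For the personalized training groups (groups 1 and 3), elbow extension will be restricted". The numbers of groups 2 and 3 are swapped between the two.

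**The concern.** The hypothesis consists of two directed comparisons, and the claim needs both. An omnibus or interaction F asks only whether the three profiles over time differ somehow. It can be significant because one comparator is worse than the other two arms, or because a comparator is better than the combined arm. It does not identify which combination is better, which is the purpose the analysis section gives it.

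With two measures both called primary and no rule for combining them, success could also be claimed on whichever one is significant, at whichever visit looks best. At stake is whether a reported positive trial means what the hypothesis says, and at what error rate.

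**Working it through.** **1. The plan's own figure.** The article gives 13 per group (alpha 5%, power 95%, effect size 2.23), raised to 18. Changes of 10° and 2° differ by 8°; if 2.23 is Cohen's d, the SD is 8/2.23 = 3.59°. An exact two-sided t test at d = 2.23 then needs 7 per arm, and the three-group ANOVA readings give 2 to 8 per group. So 13 is not reproduced. That is a separate matter; below, 18 per group is taken as given.

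**2. What a significant interaction shows.** The simulation has 18 per group, three visits correlated 0.5 (assumed) and the effect present at Post and Follow-up. Change from Pre has SD = SD_visit x sqrt(2(1 - 0.5)) = SD_visit, so d is the same on either scale. The table gives the share of trials with group x time F significant at 5% on one outcome:

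| True state | d = 0.8 | d = 1.0 | d = 1.5 |
|---|---|---|---|
| Combined arm ties with one comparator, beats the other | 70% | 90% | 99.8% |
| One comparator beats the combined arm | 70% | 90% | 99.9% |

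The hypothesis is false in both rows, yet F is usually significant. It is doing its job of detecting a difference, but not the hypothesised one.

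**3. Error rate from two primary outcomes.** One interaction test per outcome, success on either, no true effect:

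- Independent outcomes: 1 - (1 - 0.05)^2 = 9.75%. This is a ceiling, because these outcomes overlap.
- Simulated at outcome correlation 0.8: 7.6%. At 0.95: 6.7%.

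Allowing for simulation error, this is about 6.5-8%. The article gives no outcome correlation. High values are assumed because, for a given elbow range, the ratio follows from the ST angle.

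**4. The rule that matches the hypothesis.** Require both contrasts to favour the combined arm, each at two-sided 5%. If the combined arm truly equals one comparator, a joint win requires a wrong result in the favourable direction on that contrast, so its chance is at most 5%/2 = 2.5%; simulated, about 2.5%. No alpha split is needed. If any of the 2 outcomes x 2 visits = 4 cells may be used, the figure rises to about 7% (outcome correlation 0.8). The rule therefore works only with the outcome and the visit fixed.

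**5. Power of that rule at 18 per group.** Single contrast: noncentrality d x sqrt(18/2) = 3d on 34 degrees of freedom. Joint power is simulated.

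| d | Single contrast | Both contrasts |
|---|---|---|
| 2.23 | about 100% | about 100% |
| 1.5 | 99% | 98.5% |
| 1.0 | 83% | 73% |
| 0.8 | 64% | 49% |

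At the planned 8° difference, d = 1.0 means an SD of 8/1.0 = 8° and d = 0.8 an SD of 8/0.8 = 10°.

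**The case against.** The strongest reply is that a journal article condenses the plan. Follow-up contrasts, multiplicity adjustment and the decision rule commonly sit in an SAP, which is not shown, and asking which combinations do better implies pairwise follow-up. This stands as far as it goes: the absence of an adjustment method is not the point. The point rests on what the article does fix, namely two co-listed primary outcomes, no primary visit, and an ANOVA given a task its F test cannot perform.

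Four stronger readings are tempting, and the documents do not support them.

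- **Error of roughly 20% or more.** A reader might count 2 outcomes x 2 visits x 2 contrasts as eight free tests. The stated model covers all groups and visits in one interaction test per outcome, so on that reading only the second outcome inflates alpha. Counting either contrast as a win also contradicts a hypothesis that needs both.
- **The trial cannot separate personalisation from stimulation.** It can, conditionally. Two of the three comparisons differ in exactly one component. What is missing is a non-personalised + sham arm, so the effect of personalisation without a-tDCS is not estimable. The stated hypothesis does not need it.
- **The ratio will hit a floor.** The article gives no baseline thresholds from which to judge how many participants would leave the joint range.
- **The label swap will reverse the findings.** The combined arm is group 1 in both places, and the analysis section defines the ANOVA levels by name. The swap is a reporting inconsistency.

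**Conclusion.** The concern holds in a limited form. The primary outcome is two unranked, overlapping measures with no primary visit, and the stated test does not match the stated hypothesis. The mismatch is the larger problem: a significant interaction is the likely result (about 70% to over 99% of trials at d = 0.8 to 1.5) even when the combined arm ties with or loses to a comparator. The error inflation is modest, about 6.5-8% against 5%, and arises only if either outcome may carry the claim. If both outcomes had to succeed, the second would add no inflation, but the article does not say so. These figures rest on 18 per group and on assumed correlations (0.5 between visits, 0.8-0.95 between outcomes). The mismatch itself follows from the text and needs no assumption.

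**What to change.** 1. Make change in ST angle at one named visit the single primary outcome. ST angle is the only outcome used for sizing. Post fits the two-week treatment data behind the sample size, but the choice of visit is the sponsor's.
2. Prespecify two contrasts by arm name: personalised + a-tDCS versus non-personalised + a-tDCS, and personalised + a-tDCS versus personalised + sham-tDCS. Test each at two-sided 5%. The hypothesis is supported only if both are significant in favour of personalised + a-tDCS, with no alpha split.
3. Make the ratio and the other visit secondary.
4. Word the conclusions as the effect of personalisation given a-tDCS, and the effect of a-tDCS given personalised training.
5. Separately, reconcile the numbering of groups 2 and 3 between the abstract and the Intervention section.

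The cost is wording. The ratio loses primary status, and joint power is below that of a single contrast. The loss is negligible at the protocol's 2.23 read as d, but power falls to 73% at d = 1.0 and 49% at d = 0.8. Each comparator keeps one of the two active components, so the sponsor should consider whether the smaller effects are the more realistic ones.
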